#### Study outcomes

We aim to determine the reproducibility of the effectiveness of the Health TAPESTRY program, as well as the implementation in six primary care practices. All study outcomes are mapped onto the RE-AIM framework, along with the data source (EMR, self-report, or program records) in Table 3 [30].

Reach: to determine the reach of the study into the target population. Relevant client characteristics will be assessed. Additionally, the proportions of eligible patients who participate and number of volunteer visits will be reported. This data will be collected from the TAP-App and program records.

Effectiveness: the impact of Health TAPESTRY on patient outcomes. The two primary outcomes, the number of hospitalizations during the 6-month study period and total physical activity per week (described below) at 6 months, were chosen based on results from the initial RCT [24]. Number of hospitalizations will be extracted from the EMR. The reason for each hospitalization at discharge will be categorized into ambulatory care sensitive conditions or acute care conditions as used to understand the nature of hospitalizations [51–53]. Physical activity will be measured using the short form version of the International Physical Activity Questionnaire (IPAQ), using the standard methods of calculating metabolic equivalent of task (MET) [38]. Secondary outcomes will include time sitting, patient enablement, quality of life, treatment burden, disease burden, emergency room/urgent care visits, falls, medications, primary care visits, and negative effects (see Table 3 for measures).

Adoption: the proportion of physicians and health care providers who consent to participate and a description of volunteer involvement throughout the study will be reported. In addition, to assess how Health TAPESTRY is taken up as normal practice in each site, the validated Normalization Measure Development (NoMAD) survey will be used [54]. TAP-Huddle members will answer questions related to implementation processes every 3 months for 1 year.

Implementation: three different ways to understand “implementation” will be completed. First, a fidelity checklist specific to this study will be used and completed during later implementation. The two-part checklist was developed by the research team based on reviewing the fidelity literature and a team discussion about the core program components. One part of the checklist specifically assesses the functioning of the TAP-Huddle. Items were generated from reviewing the literature on “best practices” for team-based care applicable to the TAP-Huddle (communication, roles, organizational support/resources, as well as processes deemed critical to Health TAPESTRY). The second part contains items related to the 4 core parts of Health TAPESTRY. All questions are scored as yes or no. The second way we will understand implementation is by interpreting the qualitative data. Primary health care team members will be invited to participate in focus groups/interview (stratified by site and role in Health TAPESTRY) at least 6 months post-implementation. The question guide will be grounded in NPT [26, 27] and center on implementation barriers and facilitators, interprofessional teamwork, collaboration, and system navigation. All focus groups/interviews will be audio-recorded and transcribed into intelligent verbatim. Finally, the third way to understand implementation is to determine the program’s value for money in regard to costs and quality-adjusted life years (QALYs).

Maintenance: we will report the proportion of providers and patients who would suggest the program to others, each implementation site’s interest in continuing the program after the study has ended. The NoMAD survey results will reflect the normalization of Health TAPESTRY into current practice by each provider and site. It will also be used as a reflection exercise for sites throughout the study by identifying areas for improvement based on collective survey responses.

### Sample size

We estimated the sample sizes for both co-primary outcomes physical activity and number of hospitalizations for different effect sizes, based on the initial trial [24, 25], using Bonferroni adjustment [55], with *α* = 0.025 and power = 0.80, using software PASS v19.0.4 [56]. We selected the total sample sizes 488 for physical activity (corresponding to mean difference = 403 and SD = 1441) and 426 for number of hospitalizations (corresponding to mean difference = − 0.14 and SD = 0.47). Using the larger sample size estimate for physical activity and accounting for 20% lost to follow-up, we will require a sample size of 586 participants.

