### Randomization and blinding

After informed consent is obtained, participants will be randomized by a volunteer coordinator into the intervention or control group with a ratio of 1:1 using blocked randomization with variable block sizes of 2, 4, and 6 through REDCap (Version 9.3.1, Vanderbilt University) [36]. Couples who are eligible and both decide to participate in the program will be allocated to the same group by randomizing one person and allocating the second person to the same group. For the main analysis, one person’s data will be randomly selected for inclusion. The health care providers will not be blinded; however, they will only know a participant is receiving the intervention once a Health TAPESTRY report is received. The people (volunteers, researchers) involved in research outcome data collection will not be blinded.

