All analyses will be adjusted for baseline values and sites. All statistical tests will be two-sided and all *p* values will be reported to three decimal places with those less than 0.001 reported as *p* < 0.001. The criterion for statistical significance will be set a priori at alpha = 0.05 and will be adjusted using the Bonferroni method for multiple testing for the co-primary outcomes. There will be no adjustment of alpha for secondary and subgroup analyses as these are exploratory. Analyses will be performed using R v3.6.1 [61].

We will perform sensitivity analyses of the primary outcomes to assess the effectiveness of Health TAPESTRY. We will adopt per-protocol approach to assess the effect of Health TAPESTRY at 6 months. In addition, we will assess the effect of Health TAPESTRY without adjusting for sites and baseline values. We will also use zero inflated Poisson or negative binomial distribution for the count data, depending on the distribution, to assess the robustness of the results.

Implementation: as noted above, implementation is assessed in three ways. For fidelity to the program, sites will be described as either high, medium, or low adherence to the program as intended. The qualitative data centered on implementation will be analyzed using a descriptive thematic analysis [62] and organized using NVivo 12 (QSR 2018) [63]. Transcripts will be independently coded inductively by two reviewers with qualitative analysis experience using open coding. A third reviewer will complete random code checking and provide oversight to ensure trustworthiness of the data. The interview questions will serve as the coding guide for the first few transcripts. The three reviewers will discuss and create a formal coding structure and review it regularly as more transcripts are coded to begin to collapse codes into over-arching themes. The themes will be aligned with the NPT constructs [26, 27].

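### The 20% loss allowance multiplies 488 by 1.2 instead of dividing by 0.8, so 586 participants do not deliver the 488 that the 80% power claim needs

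*Protocol article*

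**What the plan says.** The Sample size section sizes the trial separately for the two co-primary outcomes with a Bonferroni-adjusted alpha, giving "0.025 and power = 0.80, using software PASS v19.0.4". For physical activity, the assumed effect is "mean difference = 403 and SD = 1441", and the resulting total is given as "We selected the total sample sizes 488 for physical activity". The corresponding total for the other outcome is "426 for number of hospitalizations".

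The section then moves from these totals to the enrolment target. "Using the larger sample size estimate for physical activity", and "accounting for 20% lost to follow-up, we will require a sample size of 586 participants". No other attrition rate or inflation rule appears anywhere in the article.

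Two further statements fix the calculation. The Data analysis section says "All statistical tests will be two-sided", and the Randomization and blinding section specifies allocation "with a ratio of 1:1 using blocked randomization".

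**The concern.** Loss to follow-up is a share of the people enrolled. To finish with 488 after losing 20%, the enrolment must satisfy N × 0.80 = 488. Adding 20% of 488 to itself answers a different question and always gives too small a number.

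The section therefore states 80% power, 20% loss and 586 participants together, and the three cannot all hold. The shortfall falls on physical activity, the outcome that sets the trial size. In the calculation as stated, that outcome has no margin beyond rounding to whole participants per arm. A reader who relies on the headline figure would believe that the trial is protected against a loss rate for which it has not been sized.

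**Working it through.** **Inputs.** From Sample size: difference 403, SD 1441, alpha 0.025, power 0.80, loss 20%; for hospitalizations, difference −0.14 and SD 0.47. From Data analysis: two-sided tests. From Randomization and blinding: 1:1 allocation.

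**Step 1: reproduce 488.** For two means with equal arms, by normal approximation:

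n per arm = 2 × (z₀.₉₈₇₅ + z₀.₈₀)² × (SD / difference)²
= 2 × (2.2414 + 0.8416)² × (1441 / 403)² = 243.1

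Rounded up, this is 244 per arm and 488 in total, an exact match. The noncentral t calculation gives 490. A one-sided test at 0.025 would give 402, so the plan's figure is the two-sided one. The 488 is thus the number needed with outcome data, before any allowance for loss.

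**Step 2: reproduce 586.**

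- 488 × 1.2 = 585.6, rounded up to 586. This matches.
- 488 / (1 − 0.20) = 610. This does not match.

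The gap is 610 − 586 = 24 participants, or 24 / 610 = 3.9% of the required number. That is too large to be rounding.

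**Step 3: what 586 delivers.**

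- At 20% loss: 586 × 0.80 = 468.8, about 469 with an observed outcome, which is 19 short of 488.
- Loss at which 488 remain: 1 − 488 / 586 = 16.7%.

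**Step 4: power at the retained number**, two-sided alpha 0.025, unadjusted comparison:

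| Outcome | Number with outcome | Normal approximation | t-test |
|---|---|---|---|
| Physical activity | 488 | 80.2% | 79.9% |
| Physical activity | 468.8 | 78.4% | 78.2% |
| Hospitalizations | 468.8 | 83.7% | 83.5% |

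As a check on the first method for physical activity at 468.8: 403 / (1441 × √(4 / 468.8)) = 3.028; 3.028 − 2.241 = 0.786; Φ(0.786) = 0.784.

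Hospitalizations are not at risk, because 469 exceeds the plan's own 426 for that outcome.

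**The case against.** The arithmetic is not in dispute; the case on the other side concerns how much it matters.

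**Baseline adjustment.** The Data analysis section adjusts every analysis for baseline values and site, and the IPAQ is collected at both time points, while 488 comes from an unadjusted formula. The article gives no baseline-to-6-month correlation, so any figure here is an assumption. Reducing the residual SD by √(1 − r²) at 469 participants, the normal approximation gives power of 78.9% for r = 0.1, 80.2% for r = 0.2, 82.5% for r = 0.3 and 89.5% for r = 0.5. A correlation of about 0.2 would offset the whole shortfall. This limits the practical consequence and it stands. It does not make 586 correct, because the stated calculation neither uses nor mentions such a gain.

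**Intention-to-treat with multiple imputation.** Randomized participants with missing outcomes stay in the primary analysis, so 469 counts those with an observed 6-month value and is not the analysis set. That clarification is fair. Imputation does not in general restore the information in outcomes that were never observed, however. The Sample size section itself inflates for loss, which treats lost participants as not contributing.

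**Couples.** Only one member of a participating couple enters the main analysis. If 586 counts both members, the usable number falls below 469. The article does not say how couples are counted and gives no couple rate, so this is conditional. Purely as an illustration, if 5% to 10% of participants were set aside as second members, 445 to 422 would remain, with about 76% to 74% power. The conclusion does not depend on this.

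**Size.** The loss is under two percentage points of power for one of two co-primary outcomes. No test, alpha or estimand changes. This also stands.

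**Conclusion.** The concern holds. The stated enrolment of 586 does not follow from 488 and a 20% loss; the figure that does is 610. The discrepancy is certain because every input is printed in one paragraph and both of the plan's numbers reproduce exactly, the second only through the wrong operation.

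The consequence is modest: power of about 78% rather than 80% for physical activity if the assumed loss occurs. This rests on the plan's difference, SD and alpha, on an unadjusted comparison, and on lost participants contributing no outcome information. It does not threaten the validity of the trial. It should still be corrected, because a headline sample size and power claim that the plan's own loss assumption contradicts is wrong as written.

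**What to change.** Restate the figure in the Sample size section in one of three ways:

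- give the requirement as 610 (488 / 0.80); or
- keep 586 and say that it preserves 488 for loss of up to 16.7%; or
- keep 586 and the 20% loss, and say that this leaves about 469 with observed 6-month physical activity and about 78% power at two-sided alpha 0.025, before any gain from baseline adjustment.

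If the sponsor wishes to rely on baseline adjustment to justify 586, the assumed correlation and its source should be stated. A sentence on whether the target counts both members of a couple would remove the remaining ambiguity.

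The second and third options cost only wording and a slightly less favourable statement. The first commits the trial to 24 more participants. The article reports that recruitment is still under way, so any of the three can be adopted before results are known.

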### Data analysis

The results will be reported according to the CONSORT extension for pragmatic randomized trials [57] and non-pharmacological interventions [58]. The mean (standard deviation) or median (first quartile, third quartile) for continuous variables, depending on the distribution, and count (percent) for categorical variables will be calculated. The description of the data analysis approach below is separated based on the RE-AIM framework for effectiveness and implementation. Note that for reach, adoption, and maintenance, the analysis approach is found in Table 3.

Effectiveness: the effectiveness of Health TAPESTRY will be assessed at 6 months. We will adopt intention-to-treat (ITT) as the primary analysis approach. Multiple imputation approach using chained equations will be used to impute the missing data [59]. We will consider the fraction of missing information and determine the number of imputations needed using the two-stage approach suggested by Hippel [60]. The pooled effect estimates along with 95% confidence intervals will be reported. The co-primary outcome of a number of hospital admission will be analyzed using the Poisson regression or negative binomial regression depending on the distribution. The incidence rate ratio along with 95% confidence interval will be reported. And the co-primary outcome physical activity will be analyzed using the multiple linear regression. The mean difference between intervention and control group along with 95% confidence intervals will be reported. The continuous outcomes (sitting, patient enablement, quality of life, treatment and disease burden scores) and the count secondary outcomes (number of falls, number of primary care visits, number of emergency room or urgent care visits, number of medications) will be analyzed using the multiple linear and Poisson regression or negative binomial regression, respectively. The mean difference and incidence rate ratio along with 95% confidence intervals will be reported for continuous and count outcomes respectively.

All analyses will be adjusted for baseline values and sites. All statistical tests will be two-sided and all *p* values will be reported to three decimal places with those less than 0.001 reported as *p* < 0.001. The criterion for statistical significance will be set a priori at alpha = 0.05 and will be adjusted using the Bonferroni method for multiple testing for the co-primary outcomes. There will be no adjustment of alpha for secondary and subgroup analyses as these are exploratory. Analyses will be performed using R v3.6.1 [61].

We will perform sensitivity analyses of the primary outcomes to assess the effectiveness of Health TAPESTRY. We will adopt per-protocol approach to assess the effect of Health TAPESTRY at 6 months. In addition, we will assess the effect of Health TAPESTRY without adjusting for sites and baseline values. We will also use zero inflated Poisson or negative binomial distribution for the count data, depending on the distribution, to assess the robustness of the results.

Implementation: as noted above, implementation is assessed in three ways. For fidelity to the program, sites will be described as either high, medium, or low adherence to the program as intended. The qualitative data centered on implementation will be analyzed using a descriptive thematic analysis [62] and organized using NVivo 12 (QSR 2018) [63]. Transcripts will be independently coded inductively by two reviewers with qualitative analysis experience using open coding. A third reviewer will complete random code checking and provide oversight to ensure trustworthiness of the data. The interview questions will serve as the coding guide for the first few transcripts. The three reviewers will discuss and create a formal coding structure and review it regularly as more transcripts are coded to begin to collapse codes into over-arching themes. The themes will be aligned with the NPT constructs [26, 27].

To assess the third part of “implementation” of RE-AIM, an economic evaluation of the trial will be conducted in accordance with Canadian and international guidelines for the conduct of economic evaluations of healthcare programs [64–66]. This 6-month trial-based economic evaluation will compare Health TAPESTRY versus usual care in terms of costs and quality-adjusted life years (QALYs) from a public payer perspective. To calculate costs associated with the intervention, healthcare resource utilization (e.g., physician visits, emergency room visits, hospital visits) captured in the EMR (Table 3) will be multiplied by their respective unit costs. Cost associated with the delivery of Health TAPESTRY will be derived from trial data. The volunteer organizations will track front-line program costs (e.g., training, transportation costs for home visit) and research team will monitor all other costs (e.g., development of material, personnel time). Every site may not implement the program exactly the same in which case any cost differences will be accounted for. To measure the impact of Health TAPESTRY and usual care on health-related quality of life, all participants will answer the EQ-5D-5L at baseline and 6 months (Tables 2 and 3). The Canadian algorithm will be used to derive the EQ-5D health utility scores [67]. QALYs will be calculated by the weighted EQ-5D health utility scores by time spent in health state using an area under the curve approach.

Differences in costs and QALYs will be determined using parametric or non-parametric tests as appropriate, and bootstrap techniques will be used to deal with sampling uncertainty and generate 95% confidence intervals [68]. Cost-effectiveness acceptability curves will be used to present the probability of Health TAPESTRY to be cost-effective at different willingness-to-pay thresholds (e.g., $50,000/QALY gained; $100,000/QALY gained) [64, 66]. Several sensitivity analyses will be conducted to explore the impact of certain assumptions (e.g., cost of implementing Health TAPESTRY) on the results. Missing data will be imputed using multiple imputations [69]. The results will be reported as per the Consolidated Health Economic Evaluation Reporting Standards (CHEERS) guidelines [70].

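### Both co-primary outcomes are tested at a Bonferroni-adjusted 0.025 but are to be reported with 95% confidence intervals, so the interval level does not match the planned test

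*Protocol article*

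**What the plan says.** All the relevant text is in the protocol article, in the Sample size and Data analysis sections.

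**Test level.** The Sample size section plans both co-primary outcomes "using Bonferroni adjustment [55], with *α* = 0.025 and power = 0.80". The Data analysis section says "All statistical tests will be two-sided" and "The criterion for statistical significance will be set a priori at alpha = 0.05", a level that "will be adjusted using the Bonferroni method for multiple testing for the co-primary outcomes". With two co-primary outcomes (number of hospitalizations and total physical activity), each is judged at 0.05 / 2 = 0.025, two-sided.

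**Interval level.** The Effectiveness paragraph of the same section fixes 95% for these estimates three times:
- after multiple imputation: "The pooled effect estimates along with 95% confidence intervals will be reported"
- for hospitalizations: "The incidence rate ratio along with 95% confidence interval will be reported"
- for physical activity: "The mean difference between intervention and control group along with 95% confidence intervals will be reported"

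The secondary outcomes also get 95% intervals. The section exempts them from alpha adjustment because they are exploratory. The article mentions no 97.5% or otherwise adjusted interval, and does not describe the 95% intervals as descriptive or unadjusted.

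**The concern.** A two-sided 95% interval excludes no effect exactly when the corresponding test has p below 0.05. The co-primary tests need p below 0.025, and the interval matching that rule is 97.5%. The article states both levels for the same two estimates, and they differ.

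If a co-primary result falls between the two levels, the report would show an interval that excludes no effect beside a conclusion of not significant. The trial's purpose is to see whether earlier findings on these two outcomes are reproduced. Whether a reader regards a finding as reproduced should not depend on reading the interval or the p-value. Because confirmatory and exploratory outcomes share one interval level, nothing in the intervals tells the reader which results were held to the stricter standard.

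**Working it through.** **Inputs from the article**
- Sample size: per-outcome α = 0.025; power 0.80; physical activity difference 403, SD 1441, total 488; hospitalizations difference −0.14, SD 0.47, total 426; 20% loss to follow-up; 586 to be recruited.
- Randomization and blinding: 1:1 allocation; for couples, one member's data are randomly selected for the main analysis.
- Data analysis: two-sided tests; overall alpha 0.05; 95% intervals.

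**Step 1. Confirm the test level from the plan's own sample sizes.** Per arm, n = 2 (SD/difference)² (z for α + z for power)², with z for 80% power = 0.842.
- Physical activity, two-sided 0.025: 2 × (1441/403)² × (2.241 + 0.842)² = 243.05, rounded up to 244 per arm, 488 in total. This is the stated figure.
- Physical activity, two-sided 0.05 (z = 1.960): 201 per arm, 402 in total. This does not reproduce it.
- Hospitalizations, two-sided 0.025: 215 per arm, 430 in total, against 426 stated (power at 426 is 0.797). Two-sided 0.05 gives 354.

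The sizes rest on a two-sided 0.025 test per outcome, in line with the stated Bonferroni rule.

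**Step 2. Compare the critical values.** A 95% interval uses 1.960; the planned test needs 2.241. The matching interval has level 1 − 0.025 = 97.5%, and is wider by 2.241 / 1.960 = 1.144, or 14.4%. For the incidence rate ratio this widening applies on the log scale.

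**Step 3. Locate the zone of disagreement.** It is |z| between 1.960 and 2.241, which is p between 0.025 and 0.05. With the planning SD and total N, SE = SD × √(4/N).
- Physical activity, N = 488: SE = 1441 × √(4/488) = 130.46. The 95% interval excludes zero beyond 1.960 × 130.46 ≈ 256; the planned test needs 2.241 × 130.46 ≈ 292.
- Hospitalizations, N = 426, mean-difference scale: SE = 0.47 × √(4/426) = 0.0455. The two limits are about 0.089 and 0.102.

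**Step 4. Probability of landing in the zone, per outcome.** Under no effect it is 0.05 − 0.025 = 0.025. At the planning effects it is Φ(2.241 − δ) − Φ(1.960 − δ), with δ = difference / SE. If 20% of 586 are lost, 0.8 × 586 = 469 remain, before one member of each couple is dropped.

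| Outcome | N | δ | Probability |
|---|---|---|---|
| Physical activity | 469 | 3.03 | 0.073 |
| Physical activity | 488 | 3.09 | 0.069 |
| Hospitalizations | 469 | 3.23 | 0.060 |
| Hospitalizations | 426 | 3.07 | 0.070 |

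**Step 5. Family-wise error, for independent outcomes.**
- The plan's rule, 0.025 each: 1 − 0.975² = 4.94% (at most 5% under any dependence).
- If a reader instead took both 95% intervals as the decision: 1 − 0.95² = 9.75% (at most 10%).

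**The case against.** The strongest reply is that nothing is wrong with the inference. The article names one decision criterion, the Bonferroni-adjusted alpha, and the sample size uses it. It says the intervals will be reported, not that they decide anything. A 95% interval is a legitimate statement of precision for one outcome, and a common level across outcomes makes their precision comparable. P-values are to be given to three decimals, so any reader can compare them with 0.025. Labelling an interval as unadjusted might also be thought a detail for the analysis plan.

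Most of this stands. A reader might infer that the plan lets family-wise error rise to 9.75%. The document does not support that: the error under the stated rule is at most 5%, and the larger figure describes only someone who uses the intervals as the test. A reader might also infer that the trial has a 6–7% chance per outcome of a discordant report whatever the truth. Those figures hold only at the full planning effects; under no effect the chance is 2.5%. The hospitalization figure is an approximation, because the planned analysis is a Poisson or negative binomial rate ratio and the article gives no rates or dispersion on that scale. The figure of 469 is derived, not stated, and the couples rule lowers it by an unknown amount.

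The appeal to the analysis plan does not remove the point. The article does not leave the interval level open. It states 95% for estimates whose test it puts at 0.025, and gives the reader nothing to reconcile the two.

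**Conclusion.** The point holds as a mismatch in reporting, for both co-primary outcomes. It is not an error in the test, the sample size or the control of type I error. It would be the same if Bonferroni were applied by doubling the p-values, since that is the same decision rule.

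Its practical size is modest: a discordant interval and decision in 2.5% of trials per outcome under no effect, and in roughly 6–7% at the planning effects. The latter rests on a normal approximation, 469 evaluable participants before the couples rule, and the mean-difference scale for hospitalizations. It is worth correcting because the article fixes both levels and the correction is very cheap.

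**What to change.** In the Effectiveness paragraph of the Data analysis section, specify 97.5% confidence intervals for the physical activity mean difference and the hospitalization incidence rate ratio, including their pooled versions after imputation. These may stand alone or beside 95% intervals labelled as not adjusted for multiplicity. State in the same place that significance for each co-primary outcome is judged at two-sided 0.025. Keep 95% intervals for the exploratory secondary outcomes.

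A lighter alternative is to keep only the 95% intervals, with that label and the statement about 0.025. This removes the ambiguity but leaves the co-primary outcomes without an interval that matches their test.

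The cost is a sentence or two of text and co-primary intervals 14.4% wider (on the log scale for the rate ratio). The number of participants, the data collected and the tests do not change.

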### Intervention

#### Procedures and data collection

A participant (termed “client” within the program), regardless of allocation, will receive a visit in their home from two volunteers at the start of the study and again 6 months later. The volunteers will collect data using structured surveys on the Health TAPESTRY web-based application (TAP-App) covering a variety of domains (i.e., physical activity, nutrition, mobility, quality of life; see Table 2). The volunteers will enter all data into the TAP-App using a tablet computer. The volunteers may return to the client’s home multiple times until all the surveys are complete. Participants may withdraw from the study at any point by informing the volunteer coordinator.

**Table 2 Tab2:** List of all TAP-App surveys

Construct *Survey name*	Survey description	Key information for TAP-Report	Intervention		Control	
			T_**0**_	T_**6**_	T_**0**_	T_**6**_
Demographic information *Custom*	Basic demographics	NA	X		X	
Quality of life* *EQ 5D-5L* [37]	Quality of life with respect to mobility, self-care, usual activities, pain, and anxiety/depression. Five answer options provided from able to/none to extremely difficult/extreme levels (scores ranges 0–1, higher scores = higher quality of life)	• Severe problems in walking about or unable to walk about • Severe problems washing or dressing self or unable to wash or dress self • Severe problems doing usual activities or unable to do usual activities • Severe pain/discomfort or extreme pain/discomfort • Severely anxious/depressed or extremely anxious/depressed	X	X	X	X
Physical activity *I**nternational Physical Activity Questionnaire (IPAQ)* *(short)* [38]*	Time spent doing physical activity per week	Calculated time in moderate and vigorous physical activity Time spent sitting in one typical day (in hours)	X	X	X	X
*Rapid Assessment of Physical Activity (RAPA)* [39]	Quick assessment of physical activity for older adults (score range 1–7, higher scores = higher physical activity)	Suboptimal physical activity (score < 6)	X	X	X	X
Enablement* *Patient Enablement Instrument (PEI)* [40]	Client’s ability to cope with, or have Control over their health after visit with health care team	NA	X	X	X	X
Treatment burden* *Multimorbidity Treatment Burden Questionnaire (MTBQ)* [41]	Level of difficulty of 10 treatment tasks (e.g., taking many medications)	NA	X	X	X	X

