### Trial status and dissemination policy

This trial is in the recruitment phase, and we expect the final 6-month follow-up visit for the intervention and control participants to occur in mid-2020. Recruitment began on March 15, 2018, and is expected to conclude at the end of January 2020. The study is using protocol version 2, dated July 2018. The results of this study will be published in peer-reviewed academic journals and presented at academic conferences. The datasets analyzed during the current study will be available from the corresponding author on reasonable request.

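### The physical activity model adjusts for baseline and site but not season of entry, so if activity is seasonal its standard errors will be slightly too wide

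*Protocol article*

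**What the plan says.** The Data analysis section assigns physical activity, a co-primary outcome, to multiple linear regression at 6 months and then fixes the covariates for everything: "All analyses will be adjusted for baseline values and sites". The one sensitivity analysis on covariates takes both terms out and adds none. Season, month and date of entry are not mentioned anywhere in the article.

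Under Procedures and data collection, every participant in either arm is visited "from two volunteers at the start of the study and again 6 months later". The Trial status section says: "Recruitment began on March 15, 2018, and is expected to conclude at the end of January 2020". The setting is six communities in Ontario, and Table 3 includes walking in the activity total. Randomization is 1:1 in blocks of 2, 4 and 6.

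Activity also sets the sample size. The Sample size section gives "total sample sizes 488 for physical activity (corresponding to mean difference = 403 and SD = 1441", against "426 for number of hospitalizations".

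**The concern.** A baseline covariate helps to the extent that it predicts the 6-month value. A six-month gap is the least favourable spacing for this if there is an annual cycle: whoever is measured near the peak at baseline is measured near the trough at follow-up. The cycle then lowers the fitted baseline slope and stays in the residual, and no other term in the model can take it up. Entry over almost two years means that all phases of the year are represented, so the variation would be real and not a constant shift.

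At stake is the width of the reported interval for the outcome that drives recruitment. The covariate set is a stated choice covering all analyses, so it is open to comment even though a separate analysis plan is not shown.

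**Working it through.** **1. The plan's own figure.** Inputs: "0.025 and power = 0.80, using software PASS v19.0.4" for alpha and power, "All statistical tests will be two-sided" for sidedness, difference 403, SD 1441.

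n per arm = 2 × ((2.2414 + 0.8416) × 1441 / 403)² = 243.05, so 244, and 2 × 244 = 488. This reproduces the stated total. The SD used is not reduced for baseline adjustment.

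**2. Completers and recruitment window.** The section states "accounting for 20% lost to follow-up, we will require a sample size of 586 participants"; 586 × 0.8 = 468.8, taken as 468. From 15 March 2018 to 31 January 2020 is 687 days, and 687 / 30.4375 = 22.6 months.

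**3. Assumed seasonal model.** The article gives no amplitude A (peak above mean, in the units of the planning SD) and no within-person correlation ρ. Assume:

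- Y0 = U0 + A cos t and Y6 = U6 − A cos t, with t spread evenly over the year
- total variance S² = 1441² = 2,076,481 at each visit
- corr(U0, U6) = ρ, so Var(U) = S² − A²/2

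Then:

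- Cov(Y0, Y6) = ρ(S² − A²/2) − A²/2, and the baseline slope is b = Cov / S²
- residual variance with baseline only: v1 = S² − Cov² / S²
- residual variance with baseline and season: v2 = (S² − A²/2)(1 − ρ²)
- the seasonal part left in Y6 − bY0 is −(1 + b)A cos t, which is larger than A whenever b > 0

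Worked case, A = 300 and ρ = 0.4:

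- A²/2 = 45,000 and Var(U) = 2,031,481
- Cov = 812,592 − 45,000 = 767,592, so b = 0.37
- v1 = 1,792,733 and v2 = 2,031,481 × 0.84 = 1,706,444
- SE = √(4v / 468), so 123.8 without season and 120.8 with it; ratio 1.025

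**4. What the blocks do.** The formula for v1 ignores the fact that blocks filled in order of entry spread both arms over the same dates. A simulation included this: six equal sites, 468 completers, blocks of 2, 4 and 6 in time order within site, uniform entry over 22.5 months, true difference 403, two-sided alpha 0.025, 6,000 runs per row. Each pair is without season, then with season.

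| A | ρ | True spread of estimate | Mean model SE | SE ratio | Power |
|---|---|---|---|---|---|
| 150 | 0.4 | 122.7, 122.5 | 122.6, 121.9 | 1.006 | 0.855, 0.857 |
| 150 | 0.6 | 106.4, 106.3 | 107.4, 106.3 | 1.010 | 0.936, 0.939 |
| 300 | 0.4 | 120.8, 120.5 | 123.8, 120.8 | 1.024 | 0.845, 0.856 |
| 300 | 0.6 | 105.0, 104.4 | 109.8, 105.4 | 1.042 | 0.931, 0.943 |
| 450 | 0.4 | 120.7, 119.6 | 125.6, 119.2 | 1.054 | 0.842, 0.872 |
| 450 | 0.6 | 107.7, 106.5 | 113.5, 104.0 | 1.092 | 0.916, 0.942 |

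The mean estimate was between 401.9 and 405.5 in every row, so there is no bias of note. A separate simulation with no treatment effect (A = 300, ρ = 0.5, one list of blocks, 4,000 runs) gave bias 2.7 and a type I error of 0.024 without season, against the nominal 0.025.

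The spread of the estimate is almost the same with or without season. What changes is the standard error the model reports.

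**The case against.** The strongest reply is that nothing here is wrong. Regression of the 6-month value on arm, baseline and site is a standard, valid analysis, and the article does not say that activity is seasonal. All of that stands, and it is why the point is an optional improvement.

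Four stronger readings are tempting, and the documents support none of them.

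- *The comparison is biased.* Both arms enter over the same dates in small blocks and are re-measured on the same schedule. The simulations show no bias.
- *The trial is underpowered, or season costs a number of extra participants.* The 488 rests on an unadjusted SD of 1441, which may already contain seasonal variation. Without season the baseline-adjusted model still reaches about 0.84 or more in every scenario above, over the planned 0.80. Scaling 488 by the ratio of residual variances would misstate the loss, because 488 is not the adjusted model's requirement and the blocks already keep the true spread down.
- *Every participant moves between high and low season.* This is so only on the calendar. With a mid-July peak and uniform entry, about 36% of entrants have |cos t| below 0.5, so their two visits differ less. Volunteers may also return several times to finish the surveys, so the gap is not exactly six months.
- *A season term would protect against 6-month visits slipping later in one arm.* A term in the date of entry cannot adjust for that.

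The largest amplitude shown, 450, means a peak-to-trough swing of 900, more than twice the target difference of 403. It is an upper illustration with no support in the article.

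**Conclusion.** The point holds as a small matter of precision. With covariates fixed at baseline and site, an annual cycle in activity would stay in the residual, and the model would not claim the balance over the calendar that the blocks provide. Reported intervals would be somewhat wider than they need be, and the test slightly conservative.

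The sizes given depend on the assumed amplitude and correlation, on a smooth annual cycle, on roughly even entry over the window, and on blocks filled in order of entry. If activity varies little by season, the gain is close to nil. Whether the separate analysis plan already adds such a term cannot be seen from the article.

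**What to change.** In the regressions for physical activity and sitting, add season of entry to baseline and site: either the sine and cosine of the calendar date of randomization, or a four-level season factor. Put the same terms in the imputation model for these outcomes. Write this down before any unblinded analysis, so that the choice cannot look driven by the result.

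The cost is one sentence and two or three degrees of freedom out of some 468 completers. No new data should be needed: the article does not say that dates are stored, but randomization runs through REDCap, so the date of randomization should be available. The sponsor should confirm this.
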